#### **6.4.3 Identification, eligibility assessment and the resident register (all residents)**

At each care home, trained staff (managers and study champions) will be asked to provide a register for all residents at the care home (section 6.4.3). The study champions will confirm which residents meet the eligibility criteria in section 5, this will form the screening log. To ensure residents are easily identifiable to care home staff, resident names will be recorded on the database which will only be visible to the care home staff and staff consenting residents (delivery teams and the central research nurse). Their name will be recorded next to a corresponding study ID, both of which are visible to the care home / consenting staff. When the data is passed to the rest of the study team, only anonymised data will be visible (only the study ID will be visible). The register will be maintained throughout the care home data collection period (see 6.8.1).

#### **6.4.4 Care home baseline data collection**

Baseline data collection will include data captured on the EoI form and the information detailed below. The care home manager will complete this using an online care home baseline data collection form. We understand some data will vary with time, and that this is essentially a baseline cross sectional survey.

Staff roles and numbers (FTE, permanent and agency); CQC rating; number and type of rooms in care home; care home ventilation policy (windows open/closed); IPC policy; care home manager and additional study champion contact details; funding (private/public); use of additional air filters in communal, staff and private bedrooms (acquired outside of the study).

For all eligible residents, regardless of consent status the following anonymised aggregate baseline data will be collected by trained staff: age; sex; ethnicity; receiving nursing care; vaccination status.

On an individual basis residents' frailty will also be assessed using the clinical frailty scale (a judgement-based frailty tool that evaluates specific domains including comorbidity, function, and cognition to generate a frailty score ranging from 1 (very fit) to 9 (terminally ill)).

Staff will be asked to complete the (optional) infection prevention and control & care home satisfaction questionnaires (see section 6.10).

We will also ask care homes to provide a copy of their local safeguarding policies for the study records.

#### **6.4.5 Randomisation and allocation specific training**

Following green light activation, and baseline data being received, the care homes will be randomised to receive either the intervention (usual care plus HEPA filters) or control (usual care) (see section 10 and 11). Randomisation will be stratified by whether they provide nursing care yes/no; and socioeconomic tertile (high/medium/low)) using a randomisation list pre-generated by a CTU statistician with no other involvement in recruitment activities.

Following randomisation, care homes will be informed of their allocation.

Intervention care homes will complete additional study training, specific to the use of devices in their care homes – e.g. installation, monitoring and maintaining air filters (according to manufacturer instructions), recording of outcomes and the arrangements for delivery of the air filters to the relevant care homes. For care homes allocated to the intervention, training will also involve discussions of where to locate communal room air filters. Staff will then begin inviting an average of 12 (maximum of 16) residents per care home to participate to receive an air filter in their private bedrooms and/or provide access to their medical records (see section 6.5) and share identifiers with the UKHSA.

In the control care homes staff will begin inviting an average of 12 (maximum of 16) residents per care home to participate provide access to their medical records (see section 6.5) and share identifiers with the UKHSA.

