| Aim                  | The overall aim is to investigate the clinical and cost effectiveness of portable HEPA air filters in reducing symptomatic winter respiratory infections (including COVID-19) in residents of older people's care homes.                                                                                                                                                                                                                                                                                                                                                                                                                                                                                                                                                                                                                                                                                                                                                                                                                                                                                                                                                                                                   |
| Trial design         | A two-arm, open controlled trial with 1:1 cluster randomisation to intervention or control at care home level, stratified by nursing care provision and socioeconomic status, with nested: mixed-method process evaluation; internal pilot (with go/no-go criteria); and health economic evaluations.                                                                                                                                                                                                                                                                                                                                                                                                                                                                                                                                                                                                                                                                                                                                                                                                                                                                                                                      |

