## **6.17 Methods/procedures to protect against other sources of bias**

Randomisation will be at care home level stratified by nursing care provision and socioeconomic status, because infection transmission occurs within care homes between staff and residents, and we anticipate individual use of air filters could benefit non-users.

To minimise post-randomisation bias, the care home/care home staff will complete baseline care home data prior to randomisation. Where possible, staff questionnaires will also be completed before data collection starts.

Previous research suggests ~30% of residents will wish to take part and ~40% will leave the care home or die during the study,(34) reflecting the frailty and vulnerability of the study population. To maintain study power, we will continually recruit new residents, resulting in an expected overall study dropout ~20%. Sensitivity analyses will be used to investigate the potential impact of this strategy, including checking for evidence of post-randomisation recruitment bias.

Primary outcome attrition will be minimised through the use of short, simple-to-complete, staff administered symptom questions.

The process evaluation will assess if use of air filters results in any unintended relaxation of infection prevention and control procedures.

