### 7.2 Consent of individual residents

A summary of the various study invitation and consent pathways are shown below in Figure 2. Individual residents selected to be approached to participate in the study will be given an AFRI Resident Information Sheet (AFRI-RIS) (for residents that have capacity to provide informed consent). If a resident is selected that does not have capacity, a suitable Consultee will be identified. These individuals will be given an AFRI - Consultee Information pack (AFRI-CIS). The information sheets provided will be specific to the allocation of the care home (Intervention or Control i.e. there will be specific information sheets described above, tailored to the study procedures taking place in the intervention and control arms

Residents will be invited to consent to:

- In both intervention and control care homes-
  - Allow access to their medical records (regarding baseline medical conditions and their treatments, and then subsequent infections, antibiotic prescribing and hospital admissions) for data collection purposes;
  - Complete study satisfaction questionnaires;
  - Allow the study team to share their identifiers with UKHSA (as described in section 6.12)
- In the intervention homes only-
  - Have an air filter in their private bedroom (with subsequent data collection about the air filter).

Informed consent will remain unless the individual requests to change permissions, in which case the relevant procedures will be followed.

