## 13 STATISTICS AND HEALTH ECONOMICS ANALYSIS

### 13.1 Main trial

#### 13.1.1 Sample size calculation

Previous research suggests ~30% of residents will wish to take part and ~40% will leave the care home or die during the study,(34) reflecting the frailty and vulnerability of the study population. To maintain study power, we will continually recruit new residents, resulting in an expected overall study data attrition of ~20%. We consider the advantages in power outweighs the potential disadvantage arising from the unblinded recruitment of a proportion of study participants.

Data are surprisingly limited(45) regarding the incidence of infections in care homes. One widely cited study suggests healthy adults experience four to six respiratory per year.(46) A recent study found UK care home residents experienced an average of one respiratory infection per annum.(34) Other studies suggest the incidence of all medically diagnosed infections range from 3 to 9.8 per 1,000 resident care days, equivalent to between 1 and 3 infections per resident per year.(45) (5) Another study suggested the incidence of all infections per resident is one to three infections per annum,(47) with around 50% considered to be respiratory.(48)

Considering these together, and based on PPI and investigator experience, we expect care home residents to experience two respiratory infections during the winter months (usually 1 Sept to 31 May = 273 days). This will be monitored closely as one of our stop/go criteria (Table 2). Our PPI group advised that a reduction of one infection would be important to residents, relatives and staff.

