Based on 90% power and an alpha of 0.05, to detect a reduction in winter respiratory infections of 1 per 242 person days from 2 to 1 per 242 person days, assuming a coefficient of variation of 0.78 to allow for between care home infection rate variation, calculated from data provided in personal communication from the PRINCESS study team,(34) a total of 74 care homes will be required. This assumes a mean cluster size of 12 for winter 3 (10 participants per care home for winters 1 & 2) and accounting for an attrition level as observed in PRINCESS,(34) and the continual recruitment strategy as described above, each cluster will provide a mean of 1920 person days of follow up. After reviewing accumulating data with the DMC and TSC on the number of follow up days, a decision was made to increase the number of care homes taking part in Winter 3 from 32 to 46 in order to achieve the number of person days required in the original calculation. This gives an approximate total of 91 care homes taking part in the study overall.

Each care home will participate for a single winter season (usually 1 Sept to 31 May). We estimate that 10 care homes will be randomised in winter 1 (the most experienced) and then 35 in winter 2 and 46 in Winter 3.

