#### 13.1.2 Data and statistical analysis

Analyses and reporting will be according to CONSORT guidelines(49) and will be pre-specified prior to the analysis in a detailed statistical analysis plan. Baseline data will be presented by trial arm, for both individual- and cluster-level characteristics, using descriptive statistics. Continuous measures will be presented using a measure of central tendency and variation as appropriate and categorical data as frequencies and percentages.

The primary effectiveness analysis will be conducted on the "consented" under the intention to treat principle (ITT) using mixed effects Poisson regression to estimate an incidence rate ratio (along with associated 95% confidence interval and p-value), comparing incidence of resident winter respiratory infection between groups. The primary analysis model will adjust for nursing care provision and deprivation tertile (stratification variables) and will include a random effect for care home to account for clustering. The use of a mixture distribution that captures the variation in rates across care-homes, and/or zero inflated models will be explored dependent on the nature of the data obtained. Robust standard errors will account for clustering if mixed effects models fail to converge.

The effect of the intervention on secondary outcomes in the "consented" will be investigated using the same analytical approach as in the primary analysis; using mixed effects regression models that are appropriate to the nature of the outcome being analysed (e.g. a logistic model for a binary outcome). Analyses will be repeated using anonymous data collected on all residents.

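### Every resident in the primary analysis set is invited after the home knows its arm, so the main rate ratio is open to differential-consent bias that Section 13.1.1 understates and the primary model does little to limit

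*Protocol*

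**What the plan says.** **Order of events.** The trial summary describes "A two-arm, open controlled trial with 1:1 cluster randomisation to intervention or control at care home level". Under Section 6.4.5 a home is randomised once its baseline data are in, is told the result, and then begins inviting residents. In intervention homes, "Staff will then begin inviting an average of 12 (maximum of 16) residents per care home to participate to receive an air filter", to give records access, or both. In control homes the request covers records access and identifier sharing only. Section 7.2 adds: "The information sheets provided will be specific to the allocation of the care home". Section 6.19 confirms that site staff and participants are not blinded.

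**Analysis.** Section 13.1.2 places the primary analysis on the consented residents, "under the intention to treat principle (ITT) using mixed effects Poisson regression to estimate an incidence rate ratio". The named adjustments are whether the home provides nursing care and its deprivation tertile, with a random effect for home. No resident characteristic is named.

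**How the risk is described.** Section 13.1.1 judges that the gain in power outweighs "the potential disadvantage arising from the unblinded recruitment of a proportion of study participants". Section 6.17 plans sensitivity analyses of the continual-recruitment strategy, "including checking for evidence of post-randomisation recruitment bias".

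**Resident data available.** In Section 6.4.4, before randomisation, residents' "frailty will also be assessed using the clinical frailty scale" one by one, while age, sex and nursing care are recorded only in aggregate. Section 6.6 collects date of birth, sex and receipt of nursing care individually for each consenter.

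**The concern.** Randomisation makes the homes comparable. It does not make the consenters comparable if consent is sought after allocation and means something different in each arm. A resident, or a consultee, who would accept a bedroom filter may not be the same kind of person as one who would agree to a notes review. If the two groups differ in infection risk, the primary rate ratio mixes that difference with the filter effect.

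Section 13.1.1 expects only about 30% of residents to take part, so there is room for acceptance to differ. The trade-off argued there also rests on a description, that only some participants are recruited unblinded, which Section 6.4.5 contradicts. Initial consenters and later replacements alike join after allocation is known. More homes do not help: they shrink the standard error around the same shift.

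**Working it through.** **1. Reproduce the sample size.** The inputs come from Section 13.1.1: "Based on 90% power and an alpha of 0.05, to detect a reduction in winter respiratory infections of 1 per 242 person days". The rates are r0 = 2/242 and r1 = 1/242, the coefficient of variation is k = 0.78, and each home gives y = 1920 person-days. Sidedness is not stated; two-sided is assumed. The Hayes–Bennett formula for unmatched clusters is

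c = 1 + (z_α/2 + z_β)² × [(r0 + r1)/y + k²(r0² + r1²)] / (r0 − r1)² = 36.94.

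That is 37 homes per arm, or 74 in total, which matches the protocol. The calculation says nothing about selection bias, but it shows that the inputs are usable.

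**2. Standard error with 91 homes.** Section 13.1.1 raises the number of homes to recover the originally required person-days. The person-days per home are then taken as 74 × 1920 / 91 = 1,561. Expected episodes per home with no effect are (2/242) × 1,561 = 12.9. With 45.5 homes per arm,

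SE(log IRR) = √[(2/12.9 + 2 × 0.78²)/45.5] = 0.174.

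**3. Effect of a difference between consenters.** Let b be the ratio of underlying risk between the two consented groups. With no filter effect, type I error = P(|Z + |ln b|/SE| > 1.96). The values of b are assumptions, since the protocol gives neither consent rates by arm nor any prognostic effect.

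| b | \|ln b\| | \|ln b\|/SE | Two-sided type I error |
|---|---|---|---|
| 0.95 | 0.051 | 0.30 | 6.0% |
| 0.90 | 0.105 | 0.61 | 9.3% |
| 0.85 | 0.163 | 0.94 | 15.5% |
| 0.80 | 0.223 | 1.29 | 25.0% |

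**4. What imbalance would produce such values.** For a binary risk factor with rate ratio R and prevalence p1 (intervention) and p0 (control) among consenters, the apparent IRR with no effect is (1 + p1(R − 1))/(1 + p0(R − 1)). R, p1 and p0 are again assumptions.

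| R | p1 vs p0 | Apparent IRR | Type I error, 91 homes |
|---|---|---|---|
| 1.5 | 40% vs 50% | 0.96 | 5.6% |
| 2 | 40% vs 50% | 0.93 | 6.8% |
| 2 | 30% vs 50% | 0.87 | 13% |
| 3 | 30% vs 50% | 0.80 | 25% |

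Reversing the imbalance gives apparent IRRs of 1.04 to 1.25. With 74 homes at 1920 person-days (SE 0.19), the four error rates are about 5.5%, 6.5%, 12% and 21%, slightly lower than with 91.

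**5. What the existing safeguards reach.**
- The random approach order (Section 6.5.1) stops staff choosing whom to invite. Staff then continue down the list past those who decline, so acceptance is uncontrolled.
- Home baseline data collected before randomisation (Section 6.17) do not bear on who consents.
- The recruitment-bias check in Section 6.17 is attached to continual recruitment and does not clearly cover the first consenters.
- The repeat analysis on anonymous data (Section 13.1.2), from about 30 randomly selected residents per home (Section 6.7), needs no consent. It is the strongest check available, but it is given no stated role as one.

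**The case against.** The protocol is not careless here. The study team sets the approach order at random, so one main route to recruitment bias is closed. Consent may be taken by trained researchers or network staff as well as home staff (Section 7.2.1). The percentage consenting is monitored (Section 16.1), and baseline characteristics are to be shown by arm. An intervention resident may agree to notes review without a filter, so the two offers overlap. The consent-free repeat analysis is already planned, and further covariates are often left to an analysis plan, which is not at hand. All of this stands, and it lowers the expected size of any bias. It does not make acceptance independent of allocation, and the covariates of the primary model are not left open: Section 13.1.2 names them.

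Two criticisms of covariate adjustment also stand. Residents who join later cannot have a frailty score from before randomisation, and with about 40% expected to leave or die these may not be few. Adjustment also removes measured imbalance only.

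A reader might infer that the main result is biased and its p-value invalid. The protocol does not support that. It shows a route to differential consent, not that it occurs, in which direction, or by how much. A reader might also conclude that the intention-to-treat label is wrong. That is a matter of preference: residents are analysed by their home's allocation, and the protocol says openly that the set is the consented residents.

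**Conclusion.** The concern holds as a risk that is understated and only partly guarded against. All consented residents are recruited after allocation is known, with arm-specific offers and information, and the primary model contains no resident-level covariate. The reference in Section 13.1.1 to a proportion of participants conflicts with Section 6.4.5.

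The size is conditional. Under assumed risk differences of 5% to 20% between consenters, type I error runs from about 6% to 25%. The moderate imbalances in step 4 (10 to 20 points on a factor with rate ratio 1.5 to 2) give about 5.5% to 13%. The upper end needs a strong factor and a large imbalance. Against the planned IRR of 0.5 the shift is modest: b = 0.90 would turn 0.50 into 0.45. It matters most if the true effect is small or absent. These figures assume two-sided 5% testing, k = 0.78 and 1,561 person-days per home.

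**What to change.** 1. **Section 13.1.2, primary model.** Add resident-level age, sex, receipt of nursing care and baseline clinical frailty score as fixed covariates. Use only frailty scores recorded before randomisation, and pre-specify the method for residents without one. State that this addresses measured imbalance only.
2. **Section 13.1.2, repeat analysis.** Name the analysis of the randomly selected residents as the pre-specified check for consent bias, reported beside the primary result. Note that it includes residents not offered a bedroom filter, so it answers a somewhat different question and a gap between the two results is not by itself proof of bias.
3. **Section 6.17.** Extend the recruitment-bias check from continual recruitment to all consented residents.
4. **Section 13.1.1.** Say that all consented residents, not a proportion, are recruited after allocation is known.

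The cost is wording in the protocol and analysis plan, because the covariates and the anonymous data are already collected. The real downside is handling missing covariates, mainly frailty in late joiners. It should also be confirmed that the individual frailty score can be linked to each consenter's study number, since Section 6.6 does not list frailty.

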### 2.3 Secondary objectives

1. To determine the effect of air filters installed in private residential, communal and staff only rooms during the winter months versus no air filters on residents':
  - a) Respiratory infections (episodesB and symptomatic daysA, B)
  - b) Fever and/or delirium and/or acute deterioration in physical ability (episodesA, B and symptomatic daysA, B)
  - c) Gastro-intestinal infection (episodesA, B & symptomatic daysA, B)
  - d) Antibiotic use (courses prescribedA/days consumedA, B)
  - e) Number of falls/near fallsA, B
  - f) Possible SARS-CoV-2 and Influenza-like illness infection episodesA, B
  - g) PCR confirmed SARS-CoV-2 infectionsA
  - h) PCR (or other test) confirmed Influenza A&B infectionsA
  - i) Other microbiologically confirmed infections including Streptococcal, Meningococcal, Respiratory Syncytial Virus, Norovirus and Human Metapneumovirus infectionsA
  - j) GP diagnosed respiratory (including COVID), gastrointestinal, skin and urinary infectionsA
  - k) Perception of care home environmentA
  - l) Hospitalisations (all cause, and potentially air filter preventable)A

A = an average of 12 (maximum 16) randomly selected residents per care home will be consented to provide permission to access medical records. In intervention care homes, these "consented" residents will also be invited to receive air filters in their private bedroom.

B = up to (approx) 30 randomly selected residents (all residents where the care home has ≤30 residents)

2. To determine the effect of air filters versus no air filters installed during winter months on staff members':
  - a) Sickness days away from work
  - b) Sickness days away from work due to respiratory infections
  - c) Sickness days away from work due to any other infection
  - d) Change over time in staff confidence in, and use of, infection prevention and control strategies.  
Perception of care home environment
3. To determine the effect of air filters versus no air filters installed during winter months on Care Homes':
  - a) Number of days experiencing PCR or other microbiologically confirmed infection outbreaks

4. To determine the cost-effectiveness of air filter use in reducing symptomatic respiratory infection episodes (to include hospital admissions, deaths and cause of death).

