| b. Assess fidelity to intervention                                                                                                                                                                                                               | Weekly CRF/eCRF and qualitative interviews                                            |

\* average of 12 (maximum 16) residents per care home will be consented (from a list selected at random) to receive a private bedroom air filter and/or medical notes review

\*\* Using UKHSA 'possible' case definitions: (i) COVID - new continuous cough OR temperature  $\geq 37.8^{\circ}\text{C}$  OR loss of, or change in, normal sense of smell or taste; and (ii) ILI - temperature  $\geq 37.8^{\circ}\text{C}$  AND one of the following: acute onset of at least one of the following respiratory symptoms (cough (with or without sputum), hoarseness, nasal discharge or congestion, shortness of breath, sore throat, wheezing, sneezing) OR an acute deterioration in physical or mental ability without other known cause.

§ Reasons for hospital admissions will be reviewed to identify those potentially considered preventable by air filters, namely: respiratory tract infections (+/- sepsis); urinary tract infections (+/- sepsis); skin and soft tissue infections (+/- sepsis); sepsis (no focus identified); trauma (+/- fracture); and major adverse cardiovascular events (MACE). MACE will be further categorised into: *arterial* (myocardial infarct, angina, new/exacerbation heart failure, transient ischaemic attack, haemorrhagic or thrombotic cerebrovascular accident) and *venous* (pulmonary embolism or deep vein thrombosis of the upper or lower limb).

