### 5.2 Care homes

#### 5.2.1 Inclusion criteria

- Capacity for  $\geq 20$  residents residing in single bedrooms\*
- Care homes which predominantly focuses on care for older people (residential home/nursing home)
- Willing to maintain a register of all residents, to be updated weekly until the end of April, after which new residents will not be invited
- Willing to invite residents to receive air filters and/or accept medical notes review until average of 12 (maximum 16) agree (the “consented”) per care home
- Willing to provide anonymised resident infection data, administer brief resident and staff questionnaires, and respond to data queries
- Care home owner permission to take part in study
- Willing to commit to installing air filters in care home if allocated to the intervention group
- Willing to commit to not installing air filters if allocated to control group

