### 6.1 Schedule of trial assessments and outcomes (overview)

Table 3, below, details the key assessments/outcome measures along with care home and participant-related procedures scheduled at various trial timepoints. The care home data collection period will be the winter months (usually defined as 1 September to 31 May assuming COVID-19 is still prevalent) during which the air filters will be switched on and anonymised infection data collected daily from all eligible residents that do not opt-out of study involvement.

To summarise, the following research activity will take place:

1. Care homes will be identified and screened
2. Care homes will sign up to take part in the trial and be randomised
3. Eligible residents will contribute baseline and follow-up data on a daily basis over the winter period (capped at approx 30 randomly selected residents for winters 2 & 3)
4. Care home staff will be invited to complete baseline and follow up questionnaires on an optional basis
5. Some care home staff, residents/consultees and residents' relatives will be invited to take part in a qualitative interview

A subgroup of residents (average of 12, maximum of 16 per care home) will be selected at random to be consented to provide permission to access medical records. In intervention care homes, these "consented" residents will also be invited to receive air filters in their private bedroom. The consent process for these residents will be detailed in section 7.

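### The entry rule for the 'consented', who form the primary analysis set, is contradictory, and section 6.4.5 read literally gives the two arms different rules

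*Protocol*

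**What the plan says.** The protocol describes entry to the 'consented' in two ways.

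- **Notes access is the condition.** Section 2.3, footnote A: "randomly selected residents per care home will be consented to provide permission to access medical records". Section 6.1 says that a subgroup "will be selected at random to be consented to provide permission to access medical records". Both then add that in intervention homes these same residents are also invited to have a bedroom filter.
- **Filter and/or notes access.** Section 6.4.5, in its paragraph on intervention homes, has staff invite residents to "receive an air filter in their private bedrooms and/or provide access to their medical records" "and share identifiers with the UKHSA". For control homes the next paragraph has staff invite "residents per care home to participate provide access to their medical records", again with identifier sharing, and offers no other route.

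The 'and/or' wording recurs in the Trial Summary, in sections 5.4 and 6.5.1, in the Table 1 footnote ("to receive a private bedroom air filter and/or medical notes review"), and in the care home criteria of section 5.2.1, where it governs who counts towards the target: "Willing to invite residents to receive air filters and/or accept medical notes review until average of 12 (maximum 16) agree".

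Section 13.1.2 runs the primary analysis on this set, "under the intention to treat principle (ITT) using mixed effects Poisson regression", and then repeats the analyses on anonymous data from all residents.

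**The concern.** If a filter alone is enough, the intervention set contains notes-acceptors plus filter-only acceptors, and the control set contains notes-acceptors only. Under section 6.5.1, a control-home resident who refuses notes access is passed over and staff move down the random list. A resident with the same attitude to notes access is therefore in or out of the primary set according to the home's allocation. This is a membership rule, so it would differ by arm even if recruitment were blinded.

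Two things would be at stake. First, the primary rate ratio would compare sets admitted under different rules. Second, filter-only residents would have no notes-based outcomes from the day they join, and at entry this gap could arise only in the intervention arm.

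**Working it through.** **1. The wording by arm**

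| Place | Applies to | Route into the 'consented' |
|---|---|---|
| 2.3 footnote A, 6.1 | both arms | notes access; filter added in intervention homes |
| 7.2 | both arms, then intervention only | notes access, questionnaires and UKHSA sharing in both arms; filter added in intervention homes |
| 6.7.2 | all consented, both arms | notes review planned, no exception stated |
| 6.4.5 | intervention homes | filter and/or notes access, and UKHSA sharing |
| 6.4.5 | control homes | notes access and UKHSA sharing |
| Trial Summary, 5.2.1, 5.4, Table 1 footnote, 6.5.1 | not split by arm | filter and/or notes review |

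Only section 6.4.5 applies the 'and/or' to intervention homes specifically and sets a different sentence beside it for control homes. That pair creates the arm difference.

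**2. Outcomes that depend on the route** (Table 1)

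- Primary outcome: daily staff case report forms, so available for filter-only residents.
- Antibiotics prescribed, diagnosed infections, hospitalisations: medical notes review, so absent for filter-only residents.
- Confirmed infections (1g to 1i): UKHSA data, with permission joined by 'and' in section 6.4.5 and sought in both arms in sections 7.1 and 7.2.
- Resource use: medical notes, care home notes or the case report form (Table 1 and section 13.1.3).

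**3. Size of the notes-based gap**

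The planned 1,002 residents split 1:1 give about 501 per arm. The filter-only share f is not in the protocol and is assumed here.

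| f | filter-only residents (501 × f) | with notes data, of 12 per home |
|---|---|---|
| 0 | 0 | 12 |
| 5% | 25 | 11.4 |
| 10% | 50 | 10.8 |
| 20% | 100 | 9.6 |
| 30% | 150 | 8.4 |

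**4. Effect on the primary rate ratio if filters do nothing**

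Let r be the infection rate of filter-only residents relative to the other consented, also assumed. The apparent rate ratio is 1 + f(r − 1).

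- f = 0: 1.00 whatever r is.
- f = 10%, r = 0.8 to 1.25: 0.98 to 1.025.
- f = 30%, r = 0.8 to 1.25: 0.94 to 1.075.
- f = 30%, r = 0.6 to 1.5: 0.88 to 1.15.

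**5. Cost of a common rule**

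First the plan's own figure. Inputs from section 13.1.1: rates λ0 = 2/242 and λ1 = 1/242 per person-day, between-home coefficient of variation k = 0.78, y = 1,920 person-days per home, 90% power, alpha 0.05 taken as two-sided. Homes per arm for unmatched cluster rates:

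c = 1 + (1.960 + 1.282)² × [(λ0 + λ1)/y + k²(λ0² + λ1²)] / (λ0 − λ1)²

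Multiplying the bracket and the denominator by 242²:

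- first term: 3 × 242/1,920 = 0.378
- second term: 0.6084 × 5 = 3.042
- denominator: 1

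So c = 1 + 10.507 × 3.420 = 36.94, which rounds up to 37 per arm and 74 in total, as the protocol states.

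Now let the intervention arm lose a share s of its person-days. Its part of the first term, 242/1,920 = 0.126, becomes 0.126/(1 − s), and power at 37 homes per arm is Φ(√(36/V) − 1.960), where V is the bracket sum.

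| s | V | power |
|---|---|---|
| 0 | 3.420 | 90.0% |
| 20% | 3.452 | 89.8% |
| 30% | 3.474 | 89.6% |

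Variation between homes dominates V, so losing some person-days within homes costs little.

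**The case against.** The strongest reply is that no filter-only group is established. Most of the 'and/or' passages describe both arms together and can be read as shorthand: filter plus notes in intervention homes, notes alone in control homes. Section 7.2 lists notes access for both arms with the filter as an addition, and does not say whether each item can be refused separately at entry. Section 6.7.2 plans notes review for all the consented. This stands as a reason not to assume that such residents exist. It does not dispose of section 6.4.5, which uses the 'and/or' for intervention homes alone.

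Safeguards also count. Section 13.1.2 repeats the analyses in all residents, a set that does not depend on this consent, and section 6.17 plans sensitivity analyses that include a check for post-randomisation recruitment bias. These mitigate part of the concern for the primary outcome. Neither states the entry rule, and the anonymous data cannot supply notes-based outcomes.

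A reader might infer that the UKHSA-based outcomes and the costs are also missing in one arm. The documents do not support that: identifier sharing is not part of the 'and/or' choice and is sought in both arms, and resource use has other sources. Nor are primary outcome data missing; the question there is comparability. The absence of a gap in control homes also holds at entry only, because section 6.15.2 lets consented residents in either arm stop notes access later.

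**Conclusion.** The contradiction is in the current text and bears on the primary analysis set. Sections 2.3 and 6.1 make notes access the condition. Section 6.4.5, read literally, admits filter-only residents in intervention homes and has no equivalent in control homes. It should be reconciled.

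The size is unknown. The filter-only share and the relative infection rate are assumptions, and a share of zero removes both effects. The widest range shown with r between 0.6 and 1.5, a factor of 0.88 to 1.15 on the rate ratio, combines the largest assumed share with the extreme values of r. At 10% and a moderate r it is 0.98 to 1.025. The firmer consequence is that any filter-only residents lack antibiotics prescribed, diagnosed infections and hospitalisations from entry, in the intervention arm only.

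A common rule would not make the two sets fully like for like. Consent follows allocation, with information sheets specific to the arm (section 7.2), and section 13.1.1 accepts unblinded recruitment of some participants as a price for power. That wider bias remains.

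**What to change.** Use one entry rule in both arms: a resident is 'consented' if they agreed to notes review, and in intervention homes the filter is an added offer. State it in the Trial Summary, the Table 1 footnote and sections 5.2.1, 5.4, 6.4.5, 6.5.1 and 13.1.2, so that they agree with sections 2.3 and 6.1. Run the primary and notes-based analyses on that set.

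Flag filter-only residents from the consent forms and report their number per home. Keep them in the all-resident analysis, and add them back to the primary set in one sensitivity analysis. If there are none, one sentence saying so closes the point.

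The cost is wording, one flag variable and a small loss of intervention person-days: on the plan's formula, from 90.0% power to 89.8% or 89.6% if 20% or 30% of those days came from filter-only residents.
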